## Abstract

**Background:**

Preterm birth (birth before 37 weeks of gestation) and its complications are the leading contributors to neonatal and under-5 mortality. The majority of neonatal deaths in Kenya and Uganda occur during the intrapartum and immediate postnatal period. This paper describes our study protocol for implementing and evaluating a package of facility-based interventions to improve care during this critical window.

**Methods/design:**

This is a pair-matched, cluster randomized controlled trial across 20 facilities in Eastern Uganda and Western Kenya. The intervention facilities receive four components: (1) strengthening of routine data collection and data use activities; (2) implementation of the WHO Safe Childbirth Checklist modified for preterm birth; (3) PRONTO simulation training and mentoring to strengthen intrapartum and immediate newborn care; and (4) support of quality improvement teams. The control facilities receive both data strengthening and introduction of the modified checklist. The primary outcome for this study is 28-day mortality rate among preterm infants. The denominator will include all live births and fresh stillbirths weighing greater than 1000 g and less than 2500 g; all live births and fresh stillbirths weighing between 2501 and 3000 g with a documented gestational age less than 37 weeks.

**Discussion:**

The results of this study will inform interventions to improve personnel and facility capacity to respond to preterm labor and delivery, as well as care for the preterm infant.

**Trial registration:**

ClinicalTrials.gov, ID: NCT03112018. Registered on 13 April 2017.

**Electronic supplementary material:**

The online version of this article (10.1186/s13063-018-2696-2) contains supplementary material, which is available to authorized users.

## Background

Preterm birth, defined by the World Health Organization (WHO) as birth before 37 weeks’ gestational age (GA), and its subsequent health complications, are the leading cause of both neonatal mortality and under-5 child mortality [1]. Globally, an estimated one million newborns die each year due to complications of prematurity, and another 0.9 million preterm survivors suffer from mild to severe neurodevelopment impairments [2]. Thus, in order to further decrease child and neonatal mortality and morbidity, averting prematurity and helping preterm infants survive and thrive must be of highest priority.

In Kenya and Uganda, annual neonatal mortality rates have slowly decreased over the last decade, but remain high at 23 and 21 per 1000 live births, respectively [3]. Preterm birth rates are estimated to be 12.3% in Kenya and 13.6% in Uganda [4]. Both countries also have estimated high rates of stillbirth (per the definition of the WHO – a baby born with no signs of life at or after 28 weeks of gestation) with 21–23 deaths per 1000 total births [5]. Stillbirths are often not measured accurately and may disguise even higher rates of prematurity and/or neonatal mortality [6].

The largest burden of both overall neonatal, and, more specifically, preterm mortality, occurs within the first 24 h of life [7]. Similarly, a large proportion of stillbirths are intrapartum deaths, occurring less than 12 h before delivery and thus resulting in infants without any signs of maceration or skin deterioration (i.e., fresh stillbirths) [6]. Thus, the intrapartum and immediate postnatal periods represent critical windows of opportunity to improve neonatal outcomes in these settings. Estimates suggest that improved facility-based care during labor and birth and immediate newborn care can avert 0.8 million newborn deaths by 2025 [7]. These estimates reflect the potential of packages of interventions, rather than a single intervention, to make significant improvements in outcomes. However, many proven interventions are not widely used in many low- and middle-income countries (LMICs). Health system bottlenecks, like financial resources and workforce capacity limitations, have constrained systems’ abilities to deliver some interventions at scale [8].

Several approaches have been shown to improve the uptake of obstetric and neonatal evidence-based practices (EBPs) and interventions. First, the WHO developed the Safe Childbirth Checklist which includes 29 EBPs that focus on maternal and neonatal outcomes at four pause points – on admission to the facility, at the time of pushing (or before cesarean delivery), soon after birth (within 1 h) and at discharge. This checklist has been used in a variety of LMICs contexts, including India, Sri Lanka, and Namibia [9–11]. In Namibia, the authors reported an increase of EBPs from 68% to 95% over a 6-month period, as well as a reduction in perinatal mortality from 22 to 13.8 deaths/1000 deliveries [11]. A more recent report from the Better Birth Trial in India revealed that despite an increase in use of EBPs, outcomes did not improve [12], suggesting that the checklist alone may be insufficient in some contexts. Data from other countries’ implementation of the Safe Childbirth Checklist are still forthcoming, with the hypothesis that checklists improve uptake of EBPs by minimizing errors of omission or reminding the target audience to perform critical steps.

Second, simulation-based training is a technique used in many fields to immerse participants in a task or setting that simulates “real-world” contexts. In the obstetrics field, PRONTO International aims to optimize care during birth, through developing and implementing innovative in situ competency-based trainings that are grounded in highly realistic obstetric and neonatal simulation training. PRONTO trainings also emphasize teamwork and communication, and kind and respectful care, which contribute to empowering teams to identify system errors to catalyze change in their facilities. Increased EBPs related to appropriate management of the third stage of labor and neonatal care were observed in intervention clinics receiving PRONTO training as compared to controls in Mexico and Guatemala [13, 14].

Third, quality improvement (QI) is a strategy to optimize processes through testing of iterative changes. QI methods to improve quality of care have been described with various frameworks, such as the Plan-Do-Study-Act cycles [15]. In resource-limited settings, QI approaches have been used to improve effective scale-up of EBPs. For example, the Project Fives Alive! is a country-wide QI project in Ghana focused on the improved delivery of maternal and child health and nutritional interventions [16]. This project brings together QI teams at each facility that are responsible for the development and testing of “change ideas.” Members of facility teams form an Improvement Collaborative Network, giving the opportunity for sharing of failures, successes and ideas. Data from this study indicate that change activities were associated with increased postnatal attendance among underweight infants [17]. However, systematic reviews have demonstrated that QI studies have modest evidence and that more studies are needed to understand the necessary and sufficient elements of QI strategies [18].

Lastly, in order to understand the impact of any interventions on maternal and neonatal outcomes, robust measurement of data must be prioritized. The Every Newborn Action Plan (ENAP) published 10 core indicators that should be tracked in order to improve quality of care for mothers and newborns [19]. This ENAP roadmap underscores the importance of standardizing indicator definitions and strengthening routine health information systems. In the field of prematurity, in particular, data strengthening around accurate GA using available resources and systems has been identified as a key issue. For example, in a study examining the use of antenatal corticosteroids in LMICs, birthweight of below the 5th percentile was used as a proxy measure for preterm birth because GA recording was considered of insufficient accuracy [20].

To our knowledge, no published studies have examined the impact of a facility-based intervention package focused on improving uptake of obstetric and neonatal EBPs in order to address preterm mortality. The East Africa Preterm Birth Initiative (PTBi-EA) hypothesizes that a facility-based intervention package administered during the intrapartum and immediate postnatal period will decrease the neonatal mortality rate among preterm neonates. Our package comprises four components: (1) strengthening of routine data collection and data use activities, including regular data quality assessments (DQAs); (2) implementation of the WHO Safe Childbirth Checklist modified for preterm birth; (3) PRONTO provider training and mentoring on key EBPs to strengthen intrapartum and immediate newborn care; and (4) support of QI teams. We believe that these interventions, in combination, will improve awareness and practice of EBPs; teamwork, communication, and respectful maternity care; and use of data for decision-making. We anticipate that results from this study will inform how interventions used in combination can improve personnel and facility capability and readiness to respond to preterm labor and delivery, as well as care for the preterm infant.

## Methods

### Trial design

This study is a pair-matched, cluster randomized controlled trial (CRCT) among 20 public sector health facilities in the Busoga Region of Uganda (four facilities) and in Migori County, Kenya (16 facilities, including 14 public facilities and two not-for-profit missionary hospitals). The full intervention package (data strengthening (DS), modified Safe Childbirth Checklist (mSCC), PRONTO provider training, and quality improvement (QI)) will be introduced to 10 facilities (intervention arm); the remaining 10 facilities will receive DS + mSCC (control arm) (Fig. 1). All facilities will begin with DS + mSCC intervention components in order to capture preliminary data for baseline and facility matching, as well as to standardize definitions of key indicators related to GA and newborn outcomes. Roll-out of mSCC and support will differ between the control and intervention sites, in that the latter will receive additional mSCC mentorship and support through synergies with PRONTO and QI. The intervention package will be delivered at the facility level, while outcomes will be measured at both an individual and facility level.

**Fig. 1 Fig1:**
[figure not shown]
Schematic of the study design

In addition to the 10 pairs of matched facilities, three referral hospitals to which the respective sub-county or district hospitals send their high-risk deliveries will receive the full intervention package. While these three referral hospitals are not included in the randomization scheme, cases referred in from any one of the 20 facilities will be included in the primary outcome analysis.

### Setting and site selection

The study regions of Migori County, Kenya and Busoga Region, Uganda were selected based on in-country stakeholder input. Prematurity burden and presence of synergistic parallel maternal/newborn research or implementation studies were considered. Health facilities were asked to participate in this study by in-country partners. Formal approval from facility leadership was obtained before any activities commenced. Given that facilities were not selected from a target population of hospitals, the intervention effects should be interpreted as impact evaluation of the intervention package implemented at the said facilities. A complete list of all facilities can be found at the clinical trial registration (ClinicalTrials.gov, ID: NCT03112018).

The Busoga Region of Eastern Uganda contains approximately three million people, or 10% of Uganda’s population, with over 80% of residents living on less than US$1 per day [21]. The estimated preterm birth rate for Uganda is 13.57% and the neonatal mortality rate is 21 per 1000 live births [3, 4]. Our selected six health facilities include approximately 22,000 deliveries per year, with 9000 deliveries from the four hospitals pair-matched in this study. Migori County, located in southwestern Kenya, has a population of approximately 917,170, wherein 43% of the population lives below the poverty line [21]. The estimated preterm birth rate for Kenya is 12.30% and the neonatal mortality rate is 23 per 1000 live births [3, 4]. Our 17 selected Migori County health facilities include approximately 10,000 deliveries per year, with 7500 deliveries at pair-matched sites.

### Study population

In all facilities, women accessing delivery care services who are admitted for labor will be eligible for this study. Anonymized data on all deliveries will be extracted from maternity registers. For follow-up, mothers of newborns who are discharged alive and born less than 2500 g or between 2501 g and 3000 g while also being identified as less than 37 weeks by recorded GA in the maternity register are being asked to participate in this study and approached for consent for follow-up for 28-day outcome. These inclusion parameters were selected based on baseline data showing a poor correlation between birthweight and reported GA in the maternity register. Women or newborns from enrolled sites who are referred to one of the three referral facilities will remain in the study. Their outcomes will be allocated to the facility to which the woman first presented.

Healthcare workers providing labor and delivery and immediate newborn care services at referral, control, and intervention facilities will participate in DS initial and refresher workshops, DQAs, as well as initial instruction and minimal refreshers or reorientation on use of the mSCC. Intervention sites will have ongoing support for mSCC utilization, in addition to the other reinforcing intervention components, PRONTO and QI. Healthcare providers in intervention facilities who provide consent for PRONTO simulation trainings will also be enrolled as study participants to ascertain changes in knowledge and practices. Facility staff in the intervention facilities will be organized into QI teams to develop and implement QI programs.

### Intervention package components

Ten intervention sites and the three referral-level hospitals will receive an intervention package comprising DS + mSCC + PRONTO + QI, while the remaining 10 control facilities will receive DS + mSCC. Each intervention component is described in detail below. The intervention package is designed to strengthen and reinforce EBPs, as well as improve teamwork, communication, respectful maternity care and data use. All study activities consist of known interventions or strategies. There are no experimental interventions that would directly impact patient safety.

#### Data strengthening (DS)

Improvements in measurement and data use in the study sites are critical to establishing baseline measures and achieving and demonstrating reductions in the burden of preterm birth. Therefore, we will begin our study by strengthening existing data collection processes in health facilities, introducing standard tools to improve GA assessment, and reviewing standardization of indicators based on national guidelines. We will also work with in-country stakeholders to develop and iterate a Data Dashboard to improve data use and dissemination of our study data (Table 1).

**Table 1 Tab1:** Components of data strengthening

Data strengthening component	Description
Reinforcing current status of data systems and indicators	We will provide technical support to standardize definitions of indicators currently being collected, improve adherence to national guidelines on labor and delivery documentation of registers, improve quality of reporting, and strengthen existing data quality assurance and data use processes. Follow-up assessments to gauge improvements in facility systems including data quality assessments (DQAs) will be conducted at regular intervals.
Refining standardized gestational age measurement	We will strengthen the use of last menstrual period (LMP) with pregnancy wheels to accurately calculate gestational age (GA). We will reinforce more accurate measures of birthweight by providing training and assessing calibration of facility scales at regular intervals.
Developing a Data Dashboard	To improve data use and dissemination of routine data, we will create a synchronized online Data Dashboard repository system that is adaptable for local providers, health officials, and national policymakers. This tool will be based on discussions among various PTBi stakeholders to better understand and respond to data needs, and is also integrated in QI and project monitoring and evaluation.

DS initial training will include review of these components with facility clinical leadership, health records officers and district staff, followed by site trainings with maternity nurses and health record staff. Refresher DS trainings will be offered as needed during the course of the study. Intermittent DQAs will be implemented every 6–12 months to collect data on specific DHIS-related indicators to assess gaps between reported and actual indicators (e.g., errors in transcription) across all control and intervention facilities. This process will also help identify barriers in the reporting processes and flow.

#### Modified Safe Childbirth Checklist

Each country team will modify the WHO Safe Childbirth Checklist in order to adhere to their national guidelines. It will be adapted to the local setting and modified to emphasize identification of preterm labor and care of the preterm infant. Specifically, we will incorporate additional elements focused on GA assessment and documentation, prematurity-related intrapartum/immediate postnatal care practices (e.g., use of magnesium sulfate, antenatal corticosteroids, immediate skin to skin, etc.). We will also include an additional pause point at initial presentation or triage (i.e., before a woman is admitted for labor), as well as prompts focused on ascertaining additional maternal demographic information, clinical risk factors and history.

Each country’s mSCC will be piloted in order to optimize content and roll-out. The mSCC will be introduced during initial DS activities at all study sites. It is intended to serve as both a decision aid for providers of key EBPs, as well as a data source for the study. An mSCC will be included in the maternity inpatient record for each woman in all control and intervention facilities.

After piloting, study data staff will review all maternity charts of cases eligible for follow-up each month and abstract a selected number of essential data variables. Study personnel will also monitor mSCC completeness and uptake by each of the five pause points either by convenience or purposive sampling. These data will be displayed on the Data Dashboard quarterly, and will allow the study teams to tailor the mSCC approach depending on uptake and use.

#### PRONTO simulation-based training

The Kenya-Uganda unified PRONTO emergency obstetric and neonatal care simulation training will emphasize the identification, triage, and management of preterm labor and birth with a curriculum specifically adapted for this context. It will include strengthening preterm labor identification with more accurate GA assessments, intrapartum care, and immediate management of fragile infants. The training also emphasizes identification and management of preeclampsia, chorioamnionitis, and other conditions related to preterm birth. The mSCC will be integrated into all PRONTO clinical activities to provide facility staff with continued opportunities to reinforce its use. Any change ideas that arise from these PRONTO activities will be integrated into QI efforts.

Selection of PRONTO mentors/trainers will be conducted in each country, with an initial pool of up to 15 candidates from which we will select the 5–10 highest performing trainers. Due to the overlapping clinical and curricular content between the two countries, refreshers will be conducted as joint facilitator training for the Kenyan mentors and Ugandan trainers. However, the training mode of delivery will vary between Kenya and Uganda. Kenya will utilize an in situ mentoring program whereby each intervention facility will receive high-intensity/4-day per week mentorship and a pair of mentors will rotate among intervention sites during the study duration. They will spend a combined total of 9–12 weeks at each intervention facility over the study duration and visits will include bedside mentoring, video-recorded, in situ simulations, knowledge reviews, skills stations, teamwork activities, and mSCC support. In Uganda, a high-intensity/shorter modular strategy will be used. A modular-based training program will be paired with 2-day-long in-situ simulation refresher and training visits. Modules and refresher/training visits will be spread out during the study period, and will similarly amount to approximately 6 weeks of mentorship. Thus, while the mode of delivery for training in each country will be different, provider teams in each country will receive approximately 56–58 h of PRONTO-based instruction using the same curriculum.

#### Quality improvement (QI) cycles

Each facility in the intervention arm will have a designated QI team comprising facility leadership, nurses, and health record staff (five to seven people). If teams have been trained previously through other QI efforts, we will revitalize and support these ongoing efforts in intervention sites. Otherwise, we will offer foundational training in QI methods. These teams will carry out Plan-Do-Study-Act cycles which include identification of a problem or bottleneck in the facility, implementation of solutions, tracking of the outcomes of the changes, and implementation or adjustment based on the results.

QI teams across facilities (known collectively as the QI collaborative) will also participate in a learning session every 3 to 6 months to discuss core learnings and QI indicators. QI indicators will be chosen by each country and will focus on EBPs expected to result in decreased neonatal mortality among preterm infants, such as uptake of Kangaroo Mother Care, antenatal corticosteroid provision, and breastfeeding. At these learning sessions, QI teams across facilities will be able to share progress on QI indicators, lessons learned, and best practices.

Elements of the package, namely PRONTO, the Data Dashboard and the mSCC, will be integrated with QI efforts. First, the Data Dashboard will help generate specific visual data to inform facility teams on progress and remaining performance gaps with respect to QI indicators and selected EBPs. Second, areas of possible improvement that arise through PRONTO mentorship and simulation will be shared with QI teams. Lastly, the mSCC may serve as a data source to document QI indicators.

### Intervention roll-out

The approach for roll-out of the intervention package will be as follows:*Baseline*: Across all selected facilities, preliminary DS with initial introduction of the mSCC will allow us to conduct a baseline survey to measure incidence of preterm births and preterm mortality in all facilities (at least 2 months). Baseline data will also be collected on key variables that are predictive/correlated with the primary outcome of mortality rate among preterm infants, including but not limited to number of deliveries, number of low birthweight babies, number of neonatal deaths, number of stillbirths, presence of a newborn corner, personnel capacity for intrapartum/postnatal care, etc.*Step 1*: Facilities will be pair-matched using key factors correlated with outcomes. Specifically, sites will be pair-matched based on variables collected during baseline that are predictive or correlated with the primary outcome of mortality rate among preterm neonates (i.e., delivery volume, number, and type of providers, facility-based neonatal mortality rate).*Step 2*: Within each matched pair, one facility will be randomized to the intervention arm and the other will be randomized to the control arm. Intervention facilities will receive PRONTO and QI interventions in addition to DS and mSCC. Randomization and allocation will be done using a computerized random number generator by the statistical team with no contact or direct interest in any specific facilities. As this is a cluster trial, there will be no blinding or allocation concealment.*Step 3*: Upon accruing sample size, the control arm facilities will be assigned to the full intervention, adding PRONTO training and QI cycles.

Figure 2 depicts the schedule of enrollment, interventions, and assessments to be conducted.

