### Data collection/quality control

For the primary outcome, existing facility-based registers will be used as primary data sources. Data entry into registries is conducted by facility care providers, as part of existing routine data collection. Information in these registries will then be extracted by study personnel. Study staff will visit each facility at least once per month to collect routine facility data from register reviews. All data will be uploaded via Open Data Kit via tablet or laptop.

For preterm babies discharged alive from hospital, mothers will be consented to be followed up by phone at 28 days following delivery. Consent of eligible mothers and their newborns will take place prior to discharge or referral. Contact information will be derived from consent forms, and from the mSCC as needed. Outcomes will be determined by targeted follow-up of study participants via phone call. Where phone calls are insufficient to trace mothers, the Kenya team will engage with community health volunteers and Uganda will employ community outreach nurses to seek out mothers.

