### Data management

Data from registries will be collected using a secure database via the Open Data Kit data entry platform and hosted on a secure server. Data will be reviewed for accuracy and completeness by a data manager before entry, and the data entry system will include automated range and logic checks to identify any data entry mistakes before they are saved. All devices used for data entry (laptops or tablets) will be encrypted and password protected.

The research team and stakeholders will have access to aggregate data across facilities through the Data Dashboard. For example, each facility will have access to their own data including 28-day outcome, but stratified data by control and intervention data will not be shared. Moreover, only the study biostatistician and core team will have access to the unblinded dataset prior to study completion.

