### Sample size and power calculations

Our primary analysis will combine data across our selected facilities in Kenya and Uganda. Since we will exclude the referral hospitals from our primary analysis, the project takes place in 20 facilities with an expected volume of 46,000 deliveries over 24 months. In an initial calculation, prior to baseline data collection, we assumed an average preterm birth rate of 12% and expected to see about 5500 preterm deliveries within this period. We assumed a 25% loss-to-follow-up rate for eligible cases. This yields at least 200 projected preterm deliveries per facility with known 28-day mortality outcome.

Detectable effect sizes were estimated by standard *t* test procedures adjusted to account for the design effect due to clustering of outcomes within facilities to attain 80% power while maintaining type I error at 5%. At a 25% 2-year cumulative incidence of 28-day mortality across both countries in the absence of the intervention, this would allow us to detect a 25% reduction in cumulative incidence if the between-cluster outcome coefficient of variation is 0.2 or below. If this coefficient increases to 0.3, we would be powered to detect a 30% reduction. If it increases to 0.4, we would be powered to detect a 40% reduction.

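### Cluster randomisation does not justify ruling out all blinding: the analyst, and in part the day-28 callers, could be masked, and the sentence does not fit the article's own restriction on an unblinded dataset

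*Protocol article*

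**What the plan says.** Step 2 under Intervention roll-out describes the randomisation within matched pairs: "Randomization and allocation will be done using a computerized random number generator by the statistical team with no contact or direct interest in any specific" site. It then adds: "As this is a cluster trial, there will be no blinding or allocation concealment". The cluster design is the only reason given.

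Data management says of arm-level results that "stratified data by control and intervention data will not be shared", and that "only the study biostatistician and core team will have access to the unblinded dataset prior to study completion".

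Data collection/quality control describes two sources for the primary outcome. Events in the facility come from registers: "Data entry into registries is conducted by facility care providers, as part of existing routine data collection". For infants discharged alive, "Outcomes will be determined by targeted follow-up of study participants via phone call". The second line is: "Where phone calls are insufficient to trace mothers, the Kenya team will engage with community health volunteers and Uganda will employ community outreach nurses". The article does not say who makes the calls or whether they know the arm.

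The sample size section adds: "We assumed a 25% loss-to-follow-up rate for eligible cases".

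**The concern.** The stated reason does not carry the conclusion. Staff and trainers in a facility know whether they received simulation training and quality improvement support, and nothing can hide that. An analyst can still work with coded arms, and a caller can still be given a list without facility or arm.

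Data management also speaks of an unblinded dataset with restricted access. That implies a masked version exists, which a blanket statement of no blinding denies. The same sentence confirms that the biostatistician sees arm-labelled data before the trial ends.

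Two things are at stake. The first is freedom in model choice: the primary analysis is a covariate-adjusted targeted maximum-likelihood estimate, with choices to make that should not be made in sight of the arm contrast. The second is ascertainment. Death is objective once known, but whether it becomes known depends on effort. Deaths before discharge are in the register, and only infants discharged alive can be lost. Unequal effort therefore changes the mix of known outcomes even if the intervention does nothing.

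**Working it through.** **The plan's own figure.** 46,000 deliveries × 0.12 = 5,520 preterm. 5,520 × (1 − 0.25) = 4,140. 4,140 / 20 = 207 per facility, which agrees with the stated minimum of 200. So the 25% loss is built into the design.

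**Inputs for the tracing check.** From the article: 28-day mortality of 25% (the sample size assumption without intervention, here applied to both arms so that there is no true effect) and loss of about 25%. Assumed, because the article does not give them:
- pre = share of eligible infants stillborn or dead before discharge: 0.10, 0.15 or 0.20
- p = share of infants discharged alive who are traced: 0.80 in intervention and 0.70 in control
- tracing unrelated to death after discharge

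**Formulas.** Risk of death after discharge: post = (0.25 − pre)/(1 − pre).
- Known outcomes only: (pre + (1 − pre)·p·post) / (pre + (1 − pre)·p)
- Untraced counted alive: pre + (1 − pre)·p·post
- Conditioning on discharge status: pre + (1 − pre)·(death rate among the traced)

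**Worked case, pre = 0.10.** post = 0.15/0.90 = 0.1667.
- Intervention: deaths 0.10 + 0.90 × 0.80 × 0.1667 = 0.220; known 0.10 + 0.72 = 0.82; rate 0.268.
- Control: deaths 0.10 + 0.90 × 0.70 × 0.1667 = 0.205; known 0.10 + 0.63 = 0.73; rate 0.281.
- Risk ratios: 0.268/0.281 = 0.955 (known only) and 0.220/0.205 = 1.073 (untraced alive).

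| pre | Tracing | RR, known only | RR, untraced alive | RR, conditioning on discharge |
|---|---|---|---|---|
| 0.10 | 80% v 70% | 0.955 | 1.073 | 1.00 |
| 0.15 | 80% v 70% | 0.938 | 1.045 | 1.00 |
| 0.20 | 80% v 70% | 0.924 | 1.021 | 1.00 |
| 0.10 | 77.5% v 72.5% | 0.977 | 1.036 | 1.00 |
| 0.15 | 77.5% v 72.5% | 0.969 | 1.022 | 1.00 |
| 0.20 | 77.5% v 72.5% | 0.961 | 1.011 | 1.00 |

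The last column is 1.00 by construction: if the traced represent all infants discharged alive, pre + (1 − pre)·post = 0.25 in each arm whatever p is.

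**If tracing is related to death.** Let untraced infants have twice the death risk of traced ones. The traced risk becomes post/(p + 2(1 − p)), that is post/1.2 in intervention and post/1.3 in control. At pre = 0.10, the conditioned rates are 0.10 + 0.90 × 0.1389 = 0.225 and 0.10 + 0.90 × 0.1282 = 0.2154, a ratio of 1.045. At pre = 0.20, they are 0.20 + 0.80 × 0.0521 = 0.2417 and 0.20 + 0.80 × 0.0481 = 0.2385, a ratio of 1.013. Conditioning then no longer removes the shift entirely.

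**Direction.** If control is traced better, every ratio inverts; for example, known-only 0.955 becomes 1/0.955 = 1.047. With equal tracing all ratios are 1.00. For scale, the design aims to detect a risk ratio of 0.75 at a between-cluster coefficient of variation of 0.2.

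**The case against.** The strongest reply is that the arithmetic shows what unequal tracing does, not what absent blinding does. That stands. Nothing in the article points to a 5- or 10-point gap, and the 25% loss is a single overall figure. A gap could also come from consent taken before discharge or from the quality of recorded contact details, and masking callers would not touch either. The two shifted columns are crude estimators. The planned targeted maximum-likelihood analysis may model missing outcomes, and its details may sit in an analysis plan not shown here.

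A second reply is that call attempts and escalation triggers belong in a full protocol or tracing manual. Their absence from a journal article is indeed no fault, and the escalation rule is worded by country with no difference by arm. The criticism is of what the article does state: a general rule against blinding, resting on a reason that does not support it.

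Three stronger readings are tempting, and the document does not support them.
- A reader might infer that there is no masking at all. Data management withholds arm-stratified results from stakeholders and limits access to the unblinded data.
- A reader might infer that allocation could be foreseen or steered. Pairing on baseline data precedes randomisation, which is done by computer by people without contact with the sites. The remark about concealment is poor wording rather than evidence of an open sequence.
- A reader might infer that callers are known to be unmasked. The article does not say who calls; this follows only from the general sentence.

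Register entries such as fresh stillbirth and gestational age are made by facility staff who know their arm. No change of wording can mask them.

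**Conclusion.** The point holds in limited form. The stated reason covers facility staff and trainers only. It does not cover the analyst or, in part, the day-28 callers, and it conflicts with the restricted unblinded dataset described under Data management. The unmasked biostatistician is stated outright and needs no assumption.

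The possible effect on the primary rate is modest and conditional. A 10-point tracing gap gives an apparent relative difference of about 4–8% on known outcomes, or 2–7% in the other direction with untraced infants counted alive. A 5-point gap gives about half of that. The planned detectable reduction is 25%. These figures assume the gap and the share of deaths before discharge. The shift disappears under conditioning on discharge status if tracing is unrelated to later death. This does not show that the result will be biased; it shows that a cheap safeguard has been set aside for a reason that does not apply to it.

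**What to change.** Replace the sentence with wording to this effect: facility staff and trainers cannot be blinded; pairs are fixed before the allocation is generated; the analyst works with coded arms until the primary model is locked; day-28 call lists omit facility and arm where feasible with existing staff; the number of call attempts and the trigger for community tracing are the same in both arms. Then amend Data management to agree, naming who holds the allocation key and who does not. Reporting the traced proportion by arm would show whether the concern arose in practice.

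Label: cheap improvement. The cost is protocol wording, a reformatted call list and a coded analysis file, with no change to sample size or care. The limits should be stated. Masking of callers is partial, since a mother may name the facility and community tracers may know it. It may need different people if the teams that visit the sites also make the calls. Coded arms are imperfect too: the statistical team generated the allocation, and facility-level covariates may identify some of the 20 sites. The common tracing rule works even where masking fails.
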